## Abstract

**Background:**

Myalgic encephalomyelitis/chronic fatigue syndrome (ME/CFS) is a common sequela following COVID-19. Although cognitive dysfunction is one of the most debilitating symptoms in ME/CFS, effective therapies are limited. Acupuncture is an important complementary and alternative therapy for ME/CFS and has been shown to have positive effects on cognitive dysfunction in other diseases. However, the effect and mechanism of acupuncture in treating cognitive dysfunction in post-COVID-19 ME/CFS(PCME/CFS) remain unclear. In this study, we designed a randomized controlled trial to evaluate the efficacy of acupuncture treatment in improving cognitive function in PCME/CFS and to investigate the neural mechanisms of acupuncture using multimodal magnetic resonance imaging (MRI) techniques.

**Methods:**

A total of 129 patients and 30 healthy controls (HCs) will be enrolled. The 129 patients with PCME/CFS will be randomly assigned in a 1:1:1 ratio to a verum acupuncture (VA), sham acupuncture (SA), or a waitlist control group. Participants in the VA and SA groups will receive three sessions of treatment per week for 8 weeks, while patients in the waitlist control group will be treated after the 8-week waiting period. The primary outcome is the change in the Symbol Digit Modalities Test (SDMT) score from baseline to week 8. The secondary outcome measures include changes from baseline to endpoint (week 8) in cognitive performance as assessed by the Digit Span Test (DST), Trail Making Test (TMT), Rey Auditory Verbal Learning Test (RAVLT), Rey–Osterrieth complex figure test (RCFT), Stroop Color and Word Test (SCWT), phonemic fluency test, category fluency test, action fluency test, and 30-item Boston Naming Test (BNT-30). In addition, changes in hippocampal metabolites and resting-state functional connectivity(RSFC) will be examined using ^1^H-magnetic resonance spectroscopy(^1^H-MRS) and functional MRI (fMRI), respectively. Moreover, the Multidimensional Fatigue Inventory (MFI-20), Pittsburgh Sleep Quality Index (PSQI), Generalized Anxiety Disorder 7-item scale (GAD-7), 24-item Hamilton Depression Scale (HAMD-24), and 36-Item Short Form Survey (SF-36) will also be assessed at baseline and week 8.

**Discussion:**

The results of this study will provide preliminary evidence regarding the efficacy of acupuncture therapy in improving cognitive function in PCME/CFS and will explore whether acupuncture improves cognitive function in this disease by modulating metabolism and RSFC in the hippocampus.

**Clinical trial registration:**

www.clinicaltrials.gov, identifier: NCT07357688.

## Introduction

Myalgic encephalomyelitis/chronic fatigue syndrome (ME/CFS) is an illness characterized by profound fatigue lasting more than 6 months, post-exertional malaise (PEM), and unrefreshing sleep (1), affecting 0.68% of adults (2). ME/CFS usually leads to substantial functional decline, which is more pronounced during episodes of PEM (3, 4). Full recovery is rare among untreated patients with ME/CFS (5).

Viral infection is an important trigger for ME/CFS, including SARS-CoV-2 (6, 7). CFS-like symptoms are common chronic manifestations following COVID-19 (8). It was found that 86.7, 72.2, and 50.5% of COVID-19 survivors experienced fatigue, PEM, and cognitive problems, respectively, 6 months after infection (9). A systematic review of 52 studies reported that 45.2% of individuals with COVID-19 had CFS-like symptom clusters 1 month after illness onset (10). The retrospective analysis of clinical manifestations in patients experiencing persisting symptoms following COVID-19 showed that 43% of patients fulfilled the National Academy of Medicine (NAM) criteria for ME/CFS 8 months after COVID-19 (11).

ME/CFS is a multisystemic illness with diverse presentations (12), and cognitive dysfunction is one of the most debilitating symptoms, with 82 and 52% of ME/CFS patients experiencing concentration and memory problems, respectively (13). Objective cognitive assessment revealed deficits in psychomotor speed and visual and verbal memory among patients with ME/CFS (13–16). In addition, the impairment of information processing efficiency in ME/CFS appeared to be comparable to that observed in multiple sclerosis (MS) (17, 18). The investigation of the trajectory of cognitive symptoms following COVID-19 demonstrated that the symptom burden seemed to increase over time, persisting for at least 3 years after infection and manifesting as both worsening and new-onset cognitive problems (19). Cognitive symptoms—including memory and word-finding difficulties and reading problems—in patients who developed ME/CFS post-COVID-19 were reported to be highly severe for more than 20 months following infection (20). Consequently, there is a pressing need to address cognitive dysfunction in post-COVID-19 ME/CFS(PCME/CFS) patients.

The pathogenesis of ME/CFS is not fully understood at present, and a line of evidence indicates that the central nervous system is involved in the pathophysiology of ME/CFS (14, 21, 22). The hippocampus, as a part of the medial temporal lobe (MTL), plays a significant role in cognitive function, such as memory formation, executive function, and reward processing (23). Hippocampal abnormalities in ME/CFS have been documented in neuroimaging research. Structural magnetic resonance imaging (MRI) has revealed increased volumes in multiple hippocampal subfields, including the left subiculum head, presubiculum head, molecular layer hippocampus head, and whole hippocampal head, among individuals with ME/CFS; moreover, these changes have been associated with fatigue, cognitive problems, unrefreshing sleep, and pain (24–26). Functional neuroimaging research showed that ME/CFS patients had impaired resting-state functional connectivity (RSFC) in the right hippocampus, and the disruption was correlated with mental fatigue (27). While completing cognitive tasks, ME/CFS patients displayed greater activation and FC in the hippocampus, suggesting the compensatory role of this region (28, 29). In addition to structural and functional changes, abnormalities in hippocampal metabolites have also been observed in ME/CFS. Brooks et al. found decreased N-acetylaspartate (NAA) concentrations in the right hippocampus of patients with ME/CFS compared to healthy controls (HCs) using ^1^H-magnetic resonance spectroscopy (^1^H-MRS) (30). Another multi-voxel ^1^H-MRS study demonstrated that increased lactate (Lac) levels in the left hippocampus were associated with fatigue in individuals with ME/CFS (31). Similarly, elevated hippocampal subfield volumes (25), altered hippocampal microstructure, and reduced RSFC of the hippocampus (32) have been observed among patients with chronic fatigue following COVID-19, indicating that the hippocampus may be involved in the pathophysiology of post-COVID-19 fatigue.

Currently, there is no known cure for ME/CFS, and a symptomatic intervention is the main principle for the treatment of this syndrome. An array of strategies has been proposed for the management of ME/CFS, such as activity management, non-steroidal anti-inflammatory drugs (NSAIDs), antipsychotics, anticonvulsants, narcotics, and antidepressants (33, 34). However, these treatments primarily target non-cognitive symptoms such as fatigue, PEM, sleep disturbance, and pain, while their effects on cognitive problems are minimal (35). The efficacy of other approaches, such as immunoregulators, energy therapy, vitamin supplements, and dietary therapy for ME/CFS, is unclear due to limited and mixed findings (12, 36).

Acupuncture is an important complementary and alternative therapy for ME/CFS. The results of a meta-analysis showed that acupuncture could significantly improve fatigue, pain, depression symptoms, and quality of life in patients with ME/CFS compared to placebo controls, whether used alone or in combination with moxibustion or rehabilitation (37–39). However, research focused on the impact of acupuncture on cognitive function in ME/CFS is limited (38), despite evidence that acupuncture treatment can significantly improve cognitive dysfunction caused by neurological or neuropsychiatric disorders such as mild cognitive impairment (MCI), stroke, and insomnia (40–42). In addition, no one has evaluated the effect of acupuncture on cognitive function in PCME/CFS.

It has been documented that acupuncture therapy treats cognitive impairment by modulating hippocampal connectivity. Functional MRI (fMRI) studies have identified increased RSFC of the hippocampus among patients with Alzheimer’s disease (AD) after 10 min of acupuncture stimulation compared to pre-acupuncture measurements (43, 44). Wei et al. (45) also found that acupuncture treatment significantly enhanced hippocampal RSFC in AD patients, which was accompanied by improvements in general cognitive function. Similarly, Wang et al. reported that acupuncture treatment improved general cognitive function in patients with subjective cognitive decline (SCD) by increasing RSFC of the hippocampus (46). A modulatory effect on cerebral metabolites has also been observed for acupuncture. The findings of ^1^H-MRS research suggested that improvements in general cognitive function, visuospatial skills, and executive function following acupuncture treatment in patients with type 2 diabetes were associated with elevated levels of *γ*-aminobutyric acid (GABA) and NAA in the left basal ganglia, as well as reduced myo-inositol (mI) concentrations in the right basal ganglia (47). Guo et al. (48) revealed that acupuncture-induced cognitive improvements in individuals with chronic partial sleep deprivation-related cognitive dysfunction were correlated with increased levels of NAA and choline (Cho), as well as decreased GABA in the basal ganglia. Moreover, Zeng et al. (49) found that acupuncture treated cognitive dysfunction in patients with gynecological cancer by increasing NAA and Cho levels in the left hippocampus. However, whether acupuncture treatment can improve cognitive function in PCME/CFS patients by modulating hippocampal RSFC and metabolites is unclear.

Accordingly, this multimodal MRI trial is designed to assess the efficacy of acupuncture treatment in improving cognitive function in PCME/CFS patients and to explore whether such improvements occur by modulating hippocampal functional connectivity and metabolism.

## Methods and analysis

### Study design

This is a prospective, three-armed randomized controlled trial using rs-fMRI and ^1^H-MRS, which will be jointly conducted by two hospitals in Chengdu. A total of 129 patients with ME/CFS occurring after COVID-19 and 30 HCs who have fully recovered from COVID-19 will be recruited. After baseline assessment, eligible patients will be randomly assigned to a verum acupuncture (VA), sham acupuncture (SA), or waitlist control group in a 1:1:1 ratio and will receive an 8-week intervention or wait. Figure 1 shows the flow chart of this trial. This study will be conducted in accordance with the Declaration of Helsinki, the Consolidated Standards of Reporting Trials (CONSORT) guidelines (50), and the Revised Standards for Reporting Interventions in Clinical Trials of Acupuncture (STRICTA) guidelines (51). This protocol has been reviewed and approved by the Ethics Committees of the Affiliated Hospital of Chengdu University of Traditional Chinese Medicine and the Public Health Clinical Center of Chengdu and has been registered at ClinicalTrials.gov (NCT07357688).

**Figure 1 fig1:**
[figure not shown]
Flow chart of study procedure.

### Recruitment

Participants in this study will be prospectively enrolled from COVID-19 survivors who were hospitalized at the Public Health Clinical Center of Chengdu between 01 January 2020 and 31 December 2023, as well as from outpatients of the Affiliated Hospital of Chengdu University of Traditional Chinese Medicine and community residents in Chengdu. For hospitalized COVID-19 survivors, preliminary screening will be performed by two appointed investigators through a telephone interview. Then, a face-to-face interview and routine blood tests will be performed to identify eligible participants. For other recruitment sources, advertisements will be disseminated both online and offline via platforms such as WeChat, websites, and others. The investigators will screen eligible participants according to inclusion and exclusion criteria. The written informed consent form will be obtained from each participant prior to formal inclusion.

#### Participants

##### Diagnostic criteria

The diagnosis of ME/CFS will be made in accordance with the criteria developed by the NAM in 2015 (1), which include the following: (1) a substantial reduction or impairment in the ability to engage in pre-illness levels of occupational, educational, social, or personal activities that persists for more than 6 months and is accompanied by fatigue, which is often profound, of new or definite onset (not lifelong), not the result of ongoing excessive exertion, and not substantially alleviated by rest; (2) post-exertional malaise; (3) unrefreshing sleep; and at least one of either (4) cognitive impairment or (5) orthostatic intolerance.

##### Inclusion criteria for patients with PCME/CFS

Participants with PCME/CFS will be included if they meet all of the following criteria: (1) 18–60 years old; (2) fatigue that occurred during or after initial recovery from COVID-19, confirmed by nasopharyngeal swab RT-PCR or antigen testing, and lasting for at least 6 months; (3) fulfillment of the NAM criteria for ME/CFS; (4) being a native Chinese speaker; (5) right-handedness; and (6) willingness to participate in the study and provision of written informed consent.

##### Exclusion criteria for patients with PCME/CFS

Individuals meeting any of the following criteria will be excluded: (1) persistent fatigue occurring prior to COVID-19 infection; (2) a previous or current diagnosis of severe chronic diseases such as heart, kidney, or liver failure or tumors; (3) a previous or current diagnosis of neurological or psychiatric disorders such as neurodegenerative disease, stroke, epilepsy, bipolar disorder, or schizophrenia; (4) a previous or current diagnosis of endocrine or metabolic diseases such as hypothyroidism, adrenocortical hypofunction, or type 2 diabetes; (5) a previous or current diagnosis of autoimmune diseases such as systemic lupus erythematosus (SLE), Sjögren’s syndrome, or rheumatoid arthritis (RA); (6) chronic infection or inflammatory diseases such as acquired immunodeficiency syndrome (AIDS), chronic hepatitis, or irritable bowel syndrome; (7) substance or alcohol abuse; (8) obesity (BMI ≥ 28); (9) long-term use of immunosuppressants or glucocorticoids; (10) major surgery within the past year; (11) presence of metal or electronic implants; (12) claustrophobia; (13) pregnancy or lactation; (14) previous acupuncture treatment within the past 3 months; and (15) participation in another clinical trial within the past month.

##### Inclusion criteria for HCs

Participants meeting all of the following criteria will be included: (1) aged 18 to 60 years old; (2) full recovery from acute COVID-19, confirmed by nasopharyngeal swab RT-PCR or antigen testing; (3) right-handedness; (4) being a native Chinese speaker; and (5) willingness to participate in the study and provision of written informed consent.

##### Exclusion criteria for HCs

Individuals meeting any of the following criteria will be excluded: (1) persistent fatigue occurring prior to COVID-19 infection; (2) a previous or current diagnosis of severe chronic diseases such as heart, kidney, or liver failure or tumors; (3) a previous or current diagnosis of neurological or psychiatric disorders such as neurodegenerative disease, stroke, epilepsy, bipolar disorder, or schizophrenia; (4) a previous or current diagnosis of endocrine or metabolic diseases such as hypothyroidism, adrenocortical hypofunction, or type 2 diabetes; (5) a previous or current diagnosis of autoimmune diseases such as systemic lupus erythematosus, Sjögren’s syndrome, or rheumatoid arthritis; (6) chronic infection or inflammatory diseases such as AIDS, chronic hepatitis, or irritable bowel syndrome; (7) substance or alcohol abuse; (8) obesity (BMI ≥ 28); (9) long-term use of immunosuppressants or glucocorticoids; (10) major surgery within the past year; (11) presence of metal or electronic implants; (12) claustrophobia; (13) pregnancy or lactation; (14) previous acupuncture treatment within the past 3 months; and (15) participation in another clinical trial within the past month.

##### Withdraw criteria

Participants meeting any of the following criteria will be withdrawn from the study: (1) poor compliance, unwillingness to continue participation, or voluntary withdrawal; (2) occurrence of serious adverse events (SAEs) or complications that make continuation of the study impossible; and (3) failure to adhere to the treatment protocol or insufficient observation data that could affect data analysis.

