##### Waitlist control group

Participants assigned to the waitlist control group will be instructed not to receive any therapy during the 8-week waiting period, but regular health follow-up through telephone will be conducted once a week by an appointed investigator. Furthermore, participants will be able to report their feelings to the investigator at any time. For those whose symptoms worsen during the waiting period, specialists at the Affiliated Hospital of Chengdu University of Traditional Chinese Medicine will be contacted immediately for symptomatic treatment, and intensive symptom monitoring will be implemented until symptoms return to their previous level. For participants whose exacerbated symptoms show no significant improvement or who develop new illnesses, withdrawal from the study will be recommended, and they will be advised to seek appropriate treatment. Participants who complete the 8-week waiting period will receive the same acupuncture treatment as the VA group for free.

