#### Outcomes

##### Primary outcome measure

The primary outcome is the change from baseline to week 8 in the SDMT score.

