#### Statistical analysis

Statistical analysis will be conducted by an appointed statistician blinded to group allocation using R software (version 4.2.1; R Foundation). Intergroup comparisons of RSFC will be performed using the DAPBI toolbox. Normally distributed continuous variables will be reported as mean±standard deviation, while non-normally distributed data will be reported as median [P25 P75]. A *p*-value of <0.05(two-tailed) will be set as the significance level for all analyses.

The intention-to-Treat (ITT) protocol will be used for the analysis of all outcomes. The ITT population will include all participants who are randomized, regardless of treatment adherence or protocol deviations. The missing value will be handled using multiple imputations.

First, intergroup comparisons of demographic data (such as age, sex, and educational level), illness duration, estimated premorbid intelligence function, and PA will be conducted to examine comparability across the three groups. Categorical data will be analyzed using the χ^2^ test. Normally distributed continuous variables will be tested using one-way analysis of variance (ANOVA), whereas the non-normally distributed data will be analyzed using the Kruskal–Wallis test.

Analysis of covariance (ANCOVA) will be applied to the primary outcome and other cognitive measures, with age, estimated premorbid intelligence ability, and PA as covariates. ANCOVA with age and PA as covariates will be used for clinical measures and brain metabolites. Repeated measures ANOVA will be used to compare differences in hippocampal functional connectivity among the three groups. Age, sex, and years of education will be included as covariates. *Post hoc* analysis will be performed for RSFC with interaction effects. Multiple comparisons for hippocampal functional connectivity will be corrected using cluster-level family-wise error (FWE) correction, with a significance threshold set at a p-value of < 0.05. The χ2 test will be used to compare the rate of AEs and SAEs between the groups. Finally, Spearman correlation analysis will be performed to examine the relationships between cognitive outcome measures and imaging indicators exhibiting intergroup differences.

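### Withdrawing non-adherent patients from the study, with no stated week-8 assessment, works against the ITT aim and may bias the primary estimate toward the effect in adherers

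*Protocol article*

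**What the plan says.** The Withdraw criteria section opens with "Participants meeting any of the following criteria will be withdrawn from the study". The first criterion is "poor compliance, unwillingness to continue participation, or voluntary withdrawal". The third is "failure to adhere to the treatment protocol or insufficient observation data that could affect data analysis". The consequence is exit from the study, not only from treatment, and the section mentions no later assessment of these patients.

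The Statistical analysis section takes the opposite stance on adherence: "The ITT population will include all participants who are randomized, regardless of treatment adherence or protocol deviations". The ITT "protocol will be used for the analysis of all outcomes", and for gaps in the data, "The missing value will be handled using multiple imputations".

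The endpoint affected is the primary one: "The primary outcome is the change from baseline to week 8 in the SDMT score". Week 8 is the end of the 24-session treatment period, or of the waiting period.

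The Waitlist control group section adds a separate exit route: "For participants whose exacerbated symptoms show no significant improvement or who develop new illnesses, withdrawal from the study will be recommended". No matching sentence appears for the verum acupuncture (VA) or sham acupuncture (SA) arms.

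**The concern.** One rule lets adherence decide who stays under observation. The other says that adherence must not affect who is analysed. A patient withdrawn for non-adherence before week 8 has no planned observed primary outcome, so the analysis has to supply one. The patients whose off-treatment week-8 values would best inform that imputation are the ones the withdrawal rule removes.

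Non-adherence is unlikely to be random here. The VA and SA arms must attend 24 clinic sessions in 8 weeks, and the Physical activity monitoring section calls physical activity a major trigger of symptom exacerbation in this disease. Missed sessions may therefore follow the course of the illness. Waitlist patients have no sessions to miss, but they have their own exit route tied to unresolved worsening or new illness. Missingness may thus differ between arms in both amount and cause.

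At stake is whether the trial estimates the effect in all randomised patients, as it says it will, or something closer to the effect in those who completed treatment.

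**Working it through.** The protocol gives no figure for the effect of withdrawal, so there is none to reproduce. The inputs are the planned mean SDMT changes in the Sample size calculation section: VA 3.75, SA 2.45, waitlist 1.30. The point does not depend on the sample size derived from them.

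**Planned differences**
- VA minus SA: 3.75 − 2.45 = 1.30
- VA minus waitlist: 3.75 − 1.30 = 2.45

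**Assumptions (mine, not the protocol's)**
- A share w of an acupuncture arm is withdrawn for non-adherence, with w from 0.10 to 0.20. The upper end uses the whole 20% dropout allowance, which the protocol does not reserve for non-adherence.
- These patients truly change like the waitlist, by 1.30.
- They are imputed like adherent patients of their own arm, whose mean is the planned one.

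**Formulae**
- Overstatement of the VA mean: w × (3.75 − 1.30) = 2.45w
- Overstatement of the SA mean: w × (2.45 − 1.30) = 1.15w
- Net overstatement of VA minus SA with equal loss: 2.45w − 1.15w = 1.30w

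| | w = 0.10 | w = 0.20 |
|---|---|---|
| VA mean overstated by | 0.245 | 0.490 |
| SA mean overstated by | 0.115 | 0.230 |
| VA − SA overstated, equal loss in both arms | 0.13 (0.13/1.30 = 10%) | 0.26 (0.26/1.30 = 20%) |
| VA − SA overstated, loss in VA only | 0.245 (0.245/1.30 = 19%) | 0.490 (0.490/1.30 = 38%) |

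**VA against waitlist.** Under these assumptions, compliance withdrawals leave the waitlist mean unchanged. The true ITT difference is (1 − w) × 3.75 + w × 1.30 − 1.30 = 2.205 at w = 0.10 and 1.96 at w = 0.20. Imputation returns about 2.45. The overstatement is 0.245 to 0.490, or 10% to 20% of 2.45.

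**Waitlist exit route.** The protocol gives no rate for it and no link between symptom worsening and SDMT, so it cannot be sized. If the patients who leave would have done worse on the SDMT, their loss would flatter the waitlist and pull the VA-waitlist contrast the other way.

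**The case against.** The strongest reply is that the two sections govern different things. The Withdraw criteria concern participation, and the Statistical analysis section defines the analysis set. A reader might infer that withdrawn patients are dropped from the ITT analysis, so that it is ITT in name only. The text does not support that: multiple imputation formally keeps them in. This part of the objection stands, and the conflict is between the follow-up rule and the ITT aim.

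It is also fair to say that the article condenses a fuller protocol. No sentence forbids a final assessment of withdrawn patients, and the imputation model, its auxiliary variables and any sensitivity analyses would normally sit in the analysis plan. So one cannot say that imputation will return adherent-like values, or that the damage is beyond repair. What survives is that the published text states a withdrawal rule. Followed as written, that rule leaves non-adherers without a week-8 value and imputation resting mainly on adherers.

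On the waitlist, withdrawal is recommended, not imposed. Its trigger is symptoms or new illness, while the outcome is an objective test of processing speed. That missingness depends on the SDMT itself is not shown; that it may relate to symptom course and differ by arm is a fair reading.

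Two smaller points stand in part. Voluntary withdrawal cannot be avoided and is not criticised here. Removing insufficient data as a ground for exit will not restore values already lost, though it stops partial missingness from becoming complete.

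**Conclusion.** The point holds as a clash between a stated withdrawal rule and the ITT aim, with possible bias toward the effect in adherers. Under the assumptions set out, the VA-SA difference is overstated by 0.13 to 0.26 points (10% to 20% of the planned 1.30) when VA and SA lose patients at the same rate. A reader might take 19% to 38% as the size, but that range needs non-adherence withdrawals in VA alone. The documents give no reason to expect this: the criteria apply to every arm, VA and SA follow the same session schedule, and participants in both are blinded. All of these figures are illustrations and not predictions. The waitlist route adds possible bias of unknown size, so the overall direction for the VA-waitlist contrast cannot be stated.

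**What to change.** The Withdraw criteria and Statistical analysis sections should be reconciled on outcome collection:

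- Separate stopping of sessions from leaving the study.
- Remove poor compliance, non-adherence to treatment and insufficient data as grounds for study withdrawal.
- Invite every randomised patient to the week-8 assessment unless they refuse further data collection. Include waitlist patients who meet the worsening or new-illness provision.
- Ask for at least the SDMT, since the full cognitive battery and MRI may be too much for some of these patients.
- Record off-treatment status, so that imputation can use it.

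Clinical care, including the arrangements for waitlist patients who worsen, is unchanged. The cost is a change of wording and some week-8 visits by patients who are off treatment. The existing daily contact for activity monitoring and the weekly waitlist calls already provide a means of inviting them. The change should be made before patients are withdrawn, because sensitivity analyses can show how far a result depends on uncollected values but cannot recover them.
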